### 9.3 *Intermediate analyses and stopping rules for futility*

**Futility:** In group A1, two intermediate analyses of mortality are planned after the 20th and 40th definitively included patients reaches Day-14 (or die prior to Day-14), respectively. Recruitment in group A1 will be stopped if the results show that the trial is unlikely to prove that mortality with favipiravir is <55%. The DSMB will be in position to recommend to stop inclusion in group A1 for futility if the number of deaths is  $\geq 14$  among first 20 patients, and  $\geq 22$  among first 40 patients in group A1.

In group A2, five intermediate analyses of mortality are planned after 20, 40, 60, 80 and 100 definitively included patients reach Day-14 (or died prior to Day-14), respectively. Recruitment in group A2 will be stopped if the results show that the trial is unlikely to prove that mortality with favipiravir is <55%. The DSMB will be in position to recommend stopping inclusion in group A2 for futility if the number of deaths is  $\geq 14, 22, 29, 36$  and  $44$  among first 20, 40, 60, 80, and 100 patients, respectively.

In group C, four intermediate analyses of mortality are planned after the 10, 20, 30 and 40 definitively included patients reaches Day-14 (or die prior to Day-14), respectively. Recruitment of children will be stopped if the results show that the trial is unlikely to prove that mortality with favipiravir is <55%. The DSMB will be in position to recommend stopping inclusion in group C for futility if the number of deaths is  $\geq 10, 14, 18$  and  $22$  among first 10, 20, 30 and 40 patients, respectively.

**Toxicity:** The Mereva CTU (*see section 8*) will make available to the DSMB members a day-by-day-standardized report of the number of patients included, dead, and alive at end of follow-up. SAE other than death will be reported to the DSMB on a weekly basis. In addition, the DSMB will receive the results of all biological tests available at each intermediate analysis. The DSMB may decide to carry out an intermediate analysis if the number of observed deaths or SAEs is higher than anticipated.

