**Blood collection:**

- Adults (groups A1 and A2): blood will be collected in 4 ml trial tubes during: (i) routine care venepuncture (Day-0; end of symptoms (EOS)+72h); (ii) additional trial venepuncture at: Day-2, Day-4, Day-13 and Day-30.
- Children (group C): blood will be collected in 4 ml trial tubes during: (i) routine care venepuncture (Day-0, EOS+72h); (ii) additional trial venepuncture at Day-2 Day-4, Day-13 and Day-30.

**Biology:** *In trial settings laboratories:* At Day-0, Day-2 Day-4, Day-13 the following tests will be done: qualitative PCR (Altona qualitative RT-PCR commercial kit); and biochemical tests (creatininemia and others tests according to local choice), if biochemical tests are doable in the laboratory. At Day-30 the following tests will be done: biochemical tests (creatininemia and others tests according to local choice) only if tests at Day-13 were abnormal *Outside trial settings laboratories:* all trial tube will be shipped frozen in triple-layer packaging to the Lyon-Mérieux BSL4 laboratory, where the following tests will be done: quantitative PCR (standard real-time RT-PCR procedures, synthetic RNA quantified external calibrators), infectious viral load (standard procedure with serial sera dilutions and infection of Vero cells), viral subpopulations (next-generation sequencing methods), drug concentrations measurement (HPLC), uricemia, and other biochemical tests (transaminases, creatininemia, natremia and kaliemia), if biochemical tests have not been done in the trial setting laboratory.

**Sample size:** recruitment in the trial will be kept opened in all groups\* until group A1 reaches 60 participants (\*unless early termination is recommended by the DSMB).

**Statistical analysis for primary outcome:** mortality by Day-14 with exact 95%CI will be reported overall and in each group separately.

In group A1, if the number of deaths is <24 (40%) out of 60 participants, the upper bound of the 95%CI will be <55%.

In group A2, if the number of deaths is <54 (45%) out of 120 participants, the upper bound of the 95%CI will be <55%.

In group C, if the number of deaths is <17 (38%) out of 45 participants, the upper bound of the 95%CI will be <55%.

In each group (A1, A2, C), we will conclude that favipiravir decreases mortality if the upper bound of the 95% CI does not include the observed pre-trial mortality (55%) in untreated patients with same duration of symptoms prior to trial initiation.

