**Statistical analysis for secondary outcomes:** mortality by Day-14 with exact 95%CI will be reported according to the second group definition (AC1, AC2, YC). In each group, we will conclude that favipiravir decreases mortality if the upper bound of the 95% CI does not include the observed pre-trial mortality (30%, 85% and 70%, respectively) in untreated patients with same characteristics prior to trial initiation.

All the following outcomes will be analysed overall and separately by the two group definitions (A1, A2, C or AC1, AC2, YC): the evolution of EBOV viral load between Day-0 and end of follow-up will be described in each patient; the numbers, proportions and exact 95% CI will be reported for grade 3-4 clinical or biological adverse events, resistance mutations and criteria for cure at Day-30; mean and inter and intra patient variability of trough concentrations of favipiravir will be described; factors associated with mortality by Day-14, cure at Day-30 and grade 3-4 clinical or biological adverse events (including evolution of viral load, time since first symptoms, trough concentrations of favipiravir) will be studied.

**Stopping rules for futility:** there will be intermediate analyses of mortality for futility only, performed every 20 adults in each group and every 10 children:

- **Adults:** recruitment in the two groups A1 and A2 will be prematurely stopped if the results show that the trial is unlikely to prove that mortality with favipiravir is <55%;

- **Children:** recruitment in the group C will be prematurely stopped if the results show that the trial is unlikely to prove that mortality with favipiravir is <55%.

**Toxicity:** deaths will be reported to the sponsor and to the DSMB on a daily basis; SAE other than death will be reported to the sponsor and to the DSMB on a weekly basis.

**Surveillance:** investigators, sponsor, SAB and DSMB will be closely coordinated, so that new facts can be discussed rapidly and the research plan (epidemiological data, design, dosage, drugs, combinations) adapted accordingly.

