### 6.3 Sample size and power

Because we expect the efficacy of the treatment to be the maximum in patients with early symptoms, the sample size calculation was based on the analysis of mortality in group A1.

The observed pre-trial mortality was estimated using the three months pre-trial data of the MSF Macenta EVD Transit Center and the MSF Gueckedou EVD Care Center from Sept 15, 2014 to Dec 14, 2015. Given those observations, and to remain pragmatic and conservative, we set the pre-trial mortality to 55% for groups A1, A2, C, and to 30%, 85%, 70% for groups AC1, AC2, YC, respectively.

With 60 participants in group A1, the power to conclude that mortality in the trial will be -20% inferior to pre-trial mortality will be equal to 89%.

Recruitment will be kept opened in all groups until 60 patients are recruited in Group A1, unless otherwise recommended by the DSMB (*see stopping rules in section 9.3*). Once 60 patients are included in Group A1, recruitment will stop in all groups, irrespective of the number of patients included in other groups. When recruitment stops, new patients who show up next will either receive favipiravir or another treatment within the framework of the next phase of the research (*see section 10*). There will be no gap between the present trial and the next phase of the research.

We estimate that 80% of adults with suspected EVD and symptoms will be confirmed to have EVD with a positive PCR. Thus, 75 patients will be eligible to group A1 (including 15 with negative PCR who will not be included, and 60 with positive PCR who will be included in analysis). The number of patients in groups A2 and C will depend on the proportion of adults showing up with  $\leq 72$ h symptoms and on the proportion of children in the population of patients with EVD referred to the three trial settings during the study period.

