## **9. Statistical analysis**

### **9.1 Mortality**

Mortality at Day-14 will be reported with its exact 95% confidence intervals (CI), overall, and separately by groups (A1, A2, C).

The analyses will be performed first using the intention to treat approach, including all patients with positive PCR who received at least one dose of favipiravir. In case of missing data for mortality at Day-14 patient will be considered dead.

A per protocol analysis will then be performed, including all patients who received the treatment until Day-9 or death.

In each group, we will conclude that favipiravir decreases mortality if the upper bound of the 95% CI does not include the observed pre-trial mortality in untreated patients with same duration of symptoms prior to trial initiation (*see section 6.3*).

In group A1, if the number of deaths is  $\leq 24$  (40%),  $\leq 19$  (32%),  $\leq 13$  (22%) or  $\leq 8$  (13%) out of 60 participants, the upper bound of the 95%CI will be  $\leq 55\%$ ,  $\leq 45\%$ ,  $\leq 35\%$  and  $\leq 25\%$ , respectively.

In group A2, if the number of deaths is  $\leq 54$  (45%),  $\leq 42$  (35%),  $\leq 31$  (26%),  $\leq 20$  (18%) out of 120 participants, the upper bound of the 95%CI will be  $\leq 55\%$ ,  $\leq 45\%$ ,  $\leq 35\%$  and  $\leq 25\%$ , respectively.

In group C, if the number of deaths is  $\leq 17$  (38%),  $\leq 13$  (29%),  $\leq 9$  (20%),  $\leq 5$  (11%) out of 45 participants, the upper bound of the 95%CI will be  $\leq 55\%$ ,  $\leq 45\%$ ,  $\leq 35\%$  and  $\leq 25\%$ , respectively.

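### The group A2 futility limits conflict with A2's success rule: 44 deaths in 100 triggers a futility stop, yet its exact upper bound (54.3%) already meets the efficacy criterion

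*Protocol*

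**What the plan says.** Section 9.3 gives the ground for stopping group A2 in words: "Recruitment in group A2 will be stopped if the results show that the trial is unlikely to prove that mortality with favipiravir is <55" per cent. It then gives the numbers: "The DSMB will be in position to recommend stopping inclusion in group A2 for futility if the number of deaths is" at least 14, 22, 29, 36 and 44 "among first 20, 40, 60, 80, and 100 patients, respectively". The Synopsis adds that "there will be intermediate analyses of mortality for futility only", so there is no early stop for efficacy.

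The success rule is in section 9.1: "we will conclude that favipiravir decreases mortality if the upper bound of the 95% CI does not include the observed pre-trial mortality". The interval is exact ("Mortality at Day-14 will be reported with its exact 95% confidence intervals (CI), overall, and separately by groups (A1, A2, C"), and section 6.3 fixes the reference value: "we set the pre-trial mortality to 55% for groups A1, A2, C". The Synopsis illustrates the rule for A2: "In group A2, if the number of deaths is <54 (45%) out of 120 participants, the upper bound of the 95%CI will be <55" per cent. Section 9.1 gives the same illustration with at most 54 deaths instead of fewer than 54. The difference does not affect this point.

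**The concern.** A futility limit should mark data from which success has become improbable. As death rates, the A2 limits are 70%, 55%, 48.3%, 45% and 44%, while the final success threshold is 54/120 = 45%. The limit therefore reaches the success rate at 80 patients and falls below it at 100. A DSMB following the table could close A2 on data that meet, or are on course to meet, the protocol's own criterion for benefit. Futility termination is one of the three trial outcomes named in the Synopsis, and section 10 says the results guide the next research phase. A group both stopped for futility and concluded to show benefit would be a result the protocol does not resolve.

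**Working it through.** **Inputs.** Reference mortality 55% (section 6.3); exact two-sided 95% interval and A2 success count of at most 54/120 (section 9.1); A2 limits 14, 22, 29, 36, 44 at 20, 40, 60, 80, 100 patients (section 9.3). The final size of 120 comes from the section 9.1 illustration.

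**Step 1: reproduce the protocol's own figure.** The Clopper-Pearson upper bound is the 0.975 quantile of Beta(x+1, n−x).
- 54/120 gives 54.35% and 55/120 gives 55.17%, so 54 is the largest success count, as stated.
- The formula also reproduces group A1 (24/60: 53.5%; 25/60: 55.1%) and group C (17/45: 53.5%; 18/45: 55.7%).

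**Step 2: apply the same rule at each A2 limit, and ask how likely success still is.** From x deaths in n, success needs at most 54−x deaths in the remaining 120−n patients. Two probabilities are shown: binomial at the observed rate x/n, and predictive with a uniform prior (beta-binomial with parameters 1+x and 1+n−x).

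| Limit | Rate | Exact upper bound | Largest success count at that n | Deaths still allowed | P(success), observed rate | P(success), predictive |
|---|---|---|---|---|---|---|
| 14/20 | 70% | 88.1% | 6 | 40 of 100 | about 0% | 0.8% |
| 22/40 | 55% | 70.7% | 15 | 32 of 80 | 0.5% | 6.8% |
| 29/60 | 48.3% | 61.6% | 24 | 25 of 60 | 18% | 26% |
| 36/80 | 45% | 56.5% | 34 | 18 of 40 | 57% | 55% |
| 44/100 | 44% | 54.3% | 44 | 10 of 20 | 78% | 76% |

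At 100 patients the futility trigger equals the largest success count. At 45/100 the upper bound is 55.3% and the success rule is no longer met.

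**Step 3: compare with group A1.** Against A1's own rule (at most 24/60), the limits 14/20 and 22/40 leave predictive probabilities of 0.06% and 0.05%. Those limits do describe futility.

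**Step 4: effect on the chance of success.** This is an exact sequential binomial calculation. Paths at or above a limit are removed at each look, and success is at most 54/120 at the end.

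| True mortality | No limits | Protocol limits followed | Same, counting a stop at exactly 44/100 as success |
|---|---|---|---|
| 35% | 99.1% | 93.7% | 94.4% |
| 40% | 88.7% | 70.2% | 73.2% |
| 42.5% | 74.2% | 51.3% | 55.2% |
| 45% | 53.8% | 32.1% | 36.1% |

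**The case against.** The arithmetic is not in dispute. The case on the other side concerns reach and weight.

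- **The strict overlap is a single cell.** Only 44/100 is both a trigger and a success. Under the listed limits, a stop at exactly that count has probability 0.7%, 3.0% and 4.0% at true mortality of 35%, 40% and 45%. This is correct, but the limit at 80 patients fails the protocol's own wording as well, because a chance above one half is not unlikely.
- **The rule is advisory.** The DSMB may recommend stopping; it is not obliged to. A recruitment stop also does not set the efficacy conclusion, and 44/100 would still pass section 9.1. This stands as a limit on the power figures, which treat the rule as followed. However, the same paragraph of section 9.3 also says recruitment will be stopped, and advisory numbers still need to match the ground given for them.
- **120 is illustrative.** Section 6.3 ends recruitment in all groups when A1 reaches 60, so A2 could finish smaller or larger. The probabilities in Steps 2 and 4 depend on 120. The conflict at 44/100 does not.
- **A2 is not the main analysis.** The trial is sized on A1, and at the 20-point effect named for A1 (35% mortality) A2 keeps 93.7%. That is so, but section 9.1 draws a conclusion in each group, A2 included.
- **The early looks are defensible.** At 20 and 40 patients the limits fit the wording, and 29/60 (18% to 26%) is arguable.

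The protocol does not derive the limits, and a statistical analysis plan not seen here may do so. No derivation could remove the conflict between sections 9.1 and 9.3 at 100 patients.

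**Conclusion.** The concern holds. At 100 patients the A2 futility trigger satisfies the A2 success rule, whatever the final group size. At 80 patients success is still more likely than not on the observed rate. If the limits are followed and A2 ends at 120, the chance of success falls by 5.4 points at 35% mortality (99.1 − 93.7), 18.5 at 40% (88.7 − 70.2), 22.9 at 42.5% (74.2 − 51.3) and 21.7 at 45% (53.8 − 32.1). Counting a stop at exactly 44/100 as success reduces these losses by about 1 to 4 points. The error lies in the looks at 80 and 100 and, less clearly, at 60. It should be corrected before the DSMB uses the table.

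**What to change.** Recompute the A2 limits from A2's own rule (at most 54/120), stopping only when the predictive probability of success is below a small value stated in section 9.3. State the assumed final size and what is concluded if A2 closes early. The threshold is the sponsor's choice. With 5% and a uniform prior, for example, the limits become at least 13, 23, 32, 41 and 49 at 20, 40, 60, 80 and 100 patients. At minimum, replace the limits at 60, 80 and 100.

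With the 5% limits the chance of success is 98.2%, 86.2%, 71.1% and 50.9% at true mortality of 35%, 40%, 42.5% and 45%. If mortality is 55% (no effect), expected A2 enrolment rises from about 49 to about 57. The chance of a false success is then 1.6%, against 1.8% with no futility looks, so the one-sided 2.5% error level still holds.

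The cost is one line in section 9.3, and in any DSMB document that repeats the numbers, plus about 8 more patients on average if the drug has no effect.

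### At the protocol's reference size of 45 children, the group C futility limit of 22 deaths in 40 is not met at 18 to 21 deaths, although success is then already impossible

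*Protocol*

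**What the plan says.** **Success rule.** Section 9.1 reports Day-14 mortality with an exact 95% confidence interval by group and states that "we will conclude that favipiravir decreases mortality if the upper bound of the 95% CI does not include the observed pre-trial mortality". Section 6.3 fixes the comparator: "we set the pre-trial mortality to 55% for groups A1, A2, C, and to 30%, 85%, 70% for groups AC1, AC2, YC, respectively". For group C, section 9.1 gives 17 or fewer deaths out of 45 as the count that keeps the upper bound at or below 55%. The Synopsis words the same limit with a strict inequality: "In group C, if the number of deaths is <17 (38%) out of 45 participants, the upper bound of the 95%CI will be <55" per cent.

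**Futility rule.** Section 9.3 plans group C looks after 10, 20, 30 and 40 children have reached Day-14 or died. The purpose is stated as "Recruitment of children will be stopped if the results show that the trial is unlikely to prove that mortality with favipiravir is <55" per cent. The DSMB may recommend stopping at 10, 14, 18 and 22 or more deaths respectively.

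**Size of group C.** Sections 6.3 and 10 keep all groups open until A1 reaches 60, so group C has no fixed size. The group C success limits are all given for 45 children, and the last planned look is at 40.

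**The concern.** A futility limit should be met no later than the point where the success criterion is out of reach, and preferably before. Here the last limit, 22, lies five deaths above the highest final count that counts as success, 17. The limits 14/20 and 22/40 are also identical in A1, A2 and C, although section 9.1 works with 60, 120 and 45 participants in these groups. The same interim count therefore leaves very different prospects in each group.

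At stake is whether the only numerical futility guidance for group C does what section 9.3 says it does. Section 2.8.2 states that no child had previously been exposed to favipiravir, so a limit that is not met once the efficacy question can no longer be answered positively deserves correction.

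**Working it through.** **Inputs.** Exact two-sided 95% interval (9.1); reference mortality 55% (6.3); success at 17 or fewer of 45 (9.1); limits 10/10, 14/20, 18/30, 22/40 (9.3). Final size 45 is an assumption, taken from 9.1. True mortalities of 35% (20 points below the reference, the effect used for A1 in 6.3), 50% and 55% are used for illustration.

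**Step 1. Reproduce the success limit.** The Clopper-Pearson upper bound for x deaths in n is the 0.975 quantile of Beta(x+1, n−x).
- 17/45: 53.5%, below 55%.
- 18/45: 55.7%, above 55%.

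So 17 is the correct limit at 45, and 18 deaths at any look rule out success.

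**Step 2. Conditional chance of success.** With x deaths at look n, this is P(Bin(45−n, p) ≤ 17−x). The table gives the highest count at which the limit is not met, with p = 35% for later children.

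| Look | Limit | Highest count not meeting it | Further deaths allowed | Chance of success |
|---|---|---|---|---|
| 10 | 10 | 9 | 8 of 35 | 8.9% |
| 20 | 14 | 13 | 4 of 25 | 3.2% |
| 30 | 18 | 17 | 0 of 15 | 0.65^15 = 0.16% |
| 40 | 22 | 21 | −4 of 5 | 0 |

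At 40, the counts 18, 19, 20 and 21 all have a chance of exactly 0 and do not meet the limit. At 30, the limit of 18 is the first count that rules out success. For comparison, 21/40 in A1 (final size 60, success at 24 or fewer) still allows 3 deaths in 20, a chance of 4.4% at 35%.

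**Step 3. How often this happens.** Exact binomial recursion through the four looks, stopping whenever a limit is met, gives the probability of passing all looks with 18 to 21 deaths at 40:
- 35% mortality: 11%
- 45%: 41%
- 50%: 45%
- 55%: 34%

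**Step 4. Change only the last limit, from 22 to 18.** At 55% mortality the stopping probabilities at 10, 20 and 30 are 0.0025, 0.1277 and 0.2377 in both cases. Expected enrolment assumes that recruitment pauses at each look.
- Current: stop at 40 is 0.2159; total 0.584. Expected enrolment 10(0.0025) + 20(0.1277) + 30(0.2377) + 40(0.2159) + 45(0.4162) = 37.1.
- With 18 at 40: stop at 40 is 0.5554; total 0.923. Expected enrolment 10(0.0025) + 20(0.1277) + 30(0.2377) + 40(0.5554) + 45(0.0767) = 35.4.
- Chance of success at 35% mortality: 0.711 in both cases, because only paths that cannot succeed are removed.

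**Step 5. Dependence on the final size.** Upper bounds are 54.6% for 18/46, 54.7% for 19/48, 54.8% for 20/50 and 54.9% for 21/52; with one child fewer each exceeds 55%. So 18, 19, 20 and 21 deaths at 40 become winnable from 46, 48, 50 and 52 children, if no further child dies. At 60 children (success at 24 or fewer), 18/40 has a 42% chance if later mortality is 35%.

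**The case against.** **Group C is not capped at 45.** If it grows beyond that, 18 to 21 deaths at 40 need not be final. This stands: impossibility holds only at the reference size, and the finding must carry that condition. It does not rescue the limits, since section 9.3 names no other size to which they belong.

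**The number of children affected is small.** At 45 it is at most five, and the expected saving at 55% mortality is 37.1 − 35.4 = 1.7. Patients count towards a look only at Day-14 or death, and no recruitment pause is stated, so some of those five may already be enrolled. This stands and lowers the severity.

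**The limits are not binding.** They let the DSMB recommend stopping; it also sees daily death counts and may call further analyses. This stands too, but these are the only numbers it is given for futility in group C.

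**Children are enrolled for more than efficacy.** Section 2.4 concedes weak paediatric power and values the safety data. That may be a reason to continue, but section 9.3 does not offer it as one.

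**Stronger readings.** A reader might infer that recruitment also continues past impossibility at 30 children. It does not: the limit there is met at 18, and 17/30 can still succeed. A reader might also infer that 14/20 and 22/40 were copied from A1. The same numbers appear in A2 as well, and the protocol gives no derivation, so their origin cannot be established.

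**Conclusion.** The contradiction between sections 9.1 and 9.3 holds at the look at 40 children, assuming a final size of 45: four possible death counts rule out success without meeting the futility limit, and at true mortalities of 45% to 55% that state is reached with probability 34% to 45%. At 30 children the fault is lateness only, since the limit acts when success is impossible and not when it is unlikely. The conclusion at 40 is the same whether success is read as 17 or fewer (9.1) or fewer than 17 (Synopsis); under the Synopsis wording 17/30 would also already have failed. Severity is moderate.

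**What to change.** Reconcile the group C limits in section 9.3 with the success rule in section 9.1, and state the final size they assume. State also that they are recalculated if the projected size of group C differs, because the group stays open until A1 reaches 60. If 45 is kept, the limit at 40 cannot exceed 18. Align the Synopsis inequality with section 9.1.

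Optionally, derive the earlier limits from a stated conditional-power threshold. For example, stopping when the chance of success is below 5% with later mortality at 35% gives 13/20 and 16/30, with 10/10 unchanged. Together with 18/40, expected enrolment at 55% mortality becomes 31.3, and the chance of success at 35% mortality goes from 0.7113 to 0.7109. Most of that further saving comes from the chosen threshold and not from correcting the contradiction.

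If the sponsor wants group C to continue for safety data whatever the efficacy outlook, section 9.3 should say so. The cost is wording in section 9.3 and in the DSMB's working documents. Correcting the limit at 40 alone costs no power.
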